### Evaluation of Training Components

#### Data Collection

Data on the measures as described in the *Measures* section will be obtained from the study practitioners before their MI training and will be collected via telephone, videoconference, or through REDCap (Research Electronic Data Capture; Vanderbilt University) or paper questionnaires. The participants will be compensated for their time to complete all data collection measures; no other financial compensation for participating in the training or implementing the study will be provided. We will use the web-based REDCap survey system or deliver paper questionnaires upon request. We will collect follow-up measures at 3 months and the end of study (at 6 months for ACHIEVE-D) and at 3 months, 6 months, and end of the study (12 months for IMPACT and RHYTHM). Continuing medical education credits will be provided to IMPACT practitioners upon the completion of 3 avatar simulations. Table 3 summarizes data collection items.

**Table 3 table3:** Study data collection.

Measure		Time point			
		Baseline (all studies)	3 months (all studies)	6 months (all studies)	12 months (IMPACT and RHYTHM)
**Demographic characteristics**					
	Age	✓			
	Gender	✓			
	Race or ethnicity	✓			
	Length of time at program	✓			
	Role in program	✓			
	Years at clinic	✓			
	Previous formal MI^a^ training	✓			
**Beliefs about MI questionnaire**					
	A 7-question survey assessing the extent to which each person agrees with statements about MI	✓	✓	✓	✓
**Importance and confidence of using MI**					
	A 6-question survey assessing the importance and confidence each person has to deliver MI	✓	✓	✓	✓
**MITI^b^ tool**					
	Validated tool used to measure fidelity to MI from standardized actor interviews.	✓	✓	✓	✓
**Avatar MI performance measurements**					
	From use of MI techniques in simulated web-based conversations	✓	✓	✓	✓
**Perceived usefulness of avatar training questionnaire**					
	A 6-question survey assessing the extent to which each person agrees with statements about the usefulness of the asynchronous avatar training			✓^c^	✓
**Interviews**					
	Semistructured interviews using a standard protocol that will elicit participants’ perceptions of real-time and avatar MI training			✓^c^	✓

^a^MI: motivational interviewing.

^b^MITI: Motivational Interviewing Treatment Integrity.

^c^Applicable to ACHIEVE-D study only.

#### Measures

We adapted the *Beliefs about Motivational Interviewing* questionnaire [43] to assess participants’ beliefs about MI. The original scale asks participants to react to 7 statements about MI on a 5-point Likert scale from “Strongly Disagree” to “Strongly Agree.” We included the following two statements in our modified version: (1) “There is strong empirical support for motivational interviewing” and (2) “I am effectively implementing motivational interviewing.”

We created a 12-item questionnaire, *Importance and Confidence to Use MI.* The participants are asked about their perspectives on the importance of, and their self-reported confidence to use, MI skills. Example questions include, “Please rate how important is it for you to use motivational interviewing” and “Please rate how confident you are in your ability to use motivational interviewing to elicit behavior change in your patient.” Responses are chosen on a 5-point Likert scale from “Not at all” to “Extremely.”

We will use the MITI tool to measure clinician fidelity to MI from audiotaped standardized patient (SP) interviews [44-46]. Correlations between practitioners’ adherence to MI with real patients and SPs are moderate to large on most indexes of performance [47]. Practitioners will conduct interviews with SP actors playing the role of patients with SMI. SP actors will talk as if they are interested in either weight loss, smoking cessation, or CVD management according to the pilot project their practitioner interviewer is implementing. MITI scores will be determined by blinded, independent coders who were trained by the tool’s creators.

A study staff member blinded to other survey measures will extract data on practitioners’ automated scores from the performance dashboard at each data collection time point as another measure of adherence to MI.

Given the novelty of the avatar training, we will also assess participants’ perceived usefulness of the avatar platform. Perceived usefulness is a key construct in the literature on technology adoption and use and refers to the extent to which a person believes that using the technology system will enhance their job performance. We adapted the Technology Acceptance Model questionnaire [48,49] to include 6 questions about the perceived usefulness of the avatar on participants’ role in the study. Responses are on a 5-point Likert scale presented as 1 (“Strongly Disagree”) to 5 (“Strongly Agree”). Example items include “I found the avatar to be useful in my role...” and “Using the avatar enhanced my effectiveness...”

We will track adherence to the following 2 training modalities: attendance at real-time training and frequency of asynchronous avatar use.

At the end of each project, we will collect qualitative data from the interviews and focus groups using a standard protocol to elicit participants’ perceptions of both the real-time and avatar MI training.

#### Analytic Plan

We will examine changes in the MITI from baseline to each subsequent time point to assess the change in practitioners’ skills in implementing MI. All SP interviews will be coded. A difference of 1 on a 5-point scale between pre- and posttraining scores for MITI global scores will be considered a clinically significant change in MI skills proficiency and will be used for statistical testing as the relevant effect size [42].

We will use a random 20-minute segment from the audiotaped SP interviews for coding as recommended by the creators of the MITI tool [42]. We will use a random calculator to ensure that the sampling of interviews that are >20 minutes is truly random so that proper inferences about the use of MI can be drawn.

We will examine changes in practitioners’ automated scores from completed avatar simulations from baseline to each follow-up time point.

We will also compare the associations of the MITI scores from the SP interviews with the Kognito-automated performance feedback metrics from a conversation simulation completed during the same time as the data collection window.

We will examine changes in participants’ beliefs about and the importance of using MI and their confidence to use its components with their patients.

Qualitative data from interviews and focus groups will be audio recorded and transcribed. Using thematic analysis [50], 2 research team members will identify meaningful segments within the responses and assign codes. We will then group these codes into themes, which will be examined by the research team.

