#### Asynchronous Avatar Training

##### Overview

The ALACRITY Center partnered with a web-based experiential learning company, Kognito [32], to develop the asynchronous avatar training. This development process with Kognito took approximately 14 months and resulted in the products described in the following sections. After the completion of their real-time MI training, the practitioners are given access to the web platform and are encouraged to register for an account that houses their study-specific avatar training and simulation. The first component is a 12-minute didactic module, “Motivational Interviewing Techniques*,”* which uses an avatar coach to provide an overview of the method. This module is identical for each of the 3 projects and must be completed before the learners move on to the second part of the training, the conversation simulation. The participants are asked to complete their first conversation simulation as soon as possible after the real-time MI training and are prompted to use the platform throughout the study period.

Each study has 1 distinct conversation simulation that addresses the project’s respective behavioral target. All conversation simulations involve 3 characters (Figure 1). The avatar practitioner character is played by the study MI learner and discusses weight loss (ACHIEVE-D), smoking cessation (IMPACT), or cholesterol reduction (RHYTHM) with an avatar patient. The avatar patient has speech that is coded to be generated automatically; when the character stops speaking, there are 3 to 4 choices presented to the learner representing options that are more or less effective when using the guiding style of MI. Table 2 shows the learner response choices for the avatar weight loss simulation.

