The avatar platform includes several feedback features to assist learners in improving their MI skills. An on-screen meter registers and reinforces practitioners’ ability to cultivate change talk, a core skill that is essential in an MI interaction [7]. For example, if the practitioner says, “You’re aware of the health effects of smoking and they worry you enough to consider quitting” and the client responds, “Yea, I think about it...I used to smoke right after a shower but now I try to go longer...,” then the meter would indicate movement toward cultivating change talk. The simulations also include occasional thought bubbles; that is, a text appears above the avatar patient’s head and allows the learners to read the patient’s unspoken thoughts from the most recent exchange. This feature is most useful when the patient responds with silence, one-word answers, or if they appear hesitant to voice confusion over what is being discussed. As the learners move through the simulation, the platform keeps a tally of each practitioner’s choice; after completing the full simulation, there is a performance dashboard available to the learner on their use of MI spirit and skills. Learners are able to see their scores on the relational components of the MI spirit (partnership and empathy); adherence to the technical aspects of the approach (cultivating change talk and softening sustain talk); and their use of specific core MI skills, questions, and reflections (Figure 2). The participants are encouraged to practice their MI skills with the avatar at least monthly throughout the study.

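### The avatar score labelled baseline can only be taken after the workshop and didactic module, so its change from baseline leaves out the initial training gain

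*Protocol article*

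**What the plan says.** **Where avatar performance is treated as a baseline measure**

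- Data Collection says that data on the measures in the Measures section "will be obtained from the study practitioners before their MI training".
- Measures includes the avatar scores: a staff member will extract "automated scores from the performance dashboard at each data collection time point as another measure of adherence to MI".
- Table 3 ticks the avatar row ("From use of MI techniques in simulated web-based conversations") at baseline for all studies, in the same column as the MITI, and again at 3, 6 and 12 months.
- The Analytic Plan then examines changes in "automated scores from completed avatar simulations from baseline to each follow-up time point".

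**What the description of the avatar training allows (Asynchronous Avatar Training, Overview)**

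- On access: "After the completion of their real-time MI training, the practitioners are given access to the web platform".
- On when the first run is expected: "The participants are asked to complete their first conversation simulation as soon as possible after the real-time MI training".
- On what comes before it: the 12-minute didactic module "must be completed before the learners move on to the second part of the training, the conversation simulation".
- On scoring: "after completing the full simulation, there is a performance dashboard available to the learner".

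**What the results are used for**

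The Abstract (Methods) plans to evaluate the impact of both training approaches on MI skills with the MITI and the avatar scores together. Strengths presents the two as ways of assessing change that results from the training. Limitations says that the pretest-posttest outcomes serve to judge both training methods.

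**The concern.** There is no comparator, so the effect of training is read from change since the pretest, and what the pretest contains decides what that change means. For the MITI, baseline precedes training. For the avatar score, the described sequence makes that impossible, yet the same word and the same table column are used for both.

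Two conclusions are at stake. First, a small, null or negative avatar change could be taken as evidence that the training did little, or that the two measures disagree, when they simply start from different points. Second, the planned association between MITI and avatar scores could, at baseline, set a pre-training MITI value against a post-workshop avatar value. That would blur any judgement of how well the automated score tracks the MITI.

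**Working it through.** The article states no figure to reproduce on this point. The check concerns the order of events and what each change score then contains.

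**Step 1. Order of events as written**

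1. Baseline data collection, before MI training (Data Collection).
2. Real-time workshop of 1, 2 or 4 hours, depending on project and role (Table 1).
3. Platform access (avatar Overview).
4. Didactic module, compulsory before the simulation (avatar Overview).
5. First conversation simulation, requested soon after the workshop (avatar Overview).
6. First dashboard score, once the full simulation is finished (avatar Overview).

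An avatar score cannot exist before step 6, whereas Data Collection and Table 3 place one at step 1. No pre-training avatar run is described, and baseline is not redefined for this measure. The two accounts cannot both hold.

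**Step 2. What each change score contains**

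Let w be the gain from workshop plus module that is present at the first simulation, and a the net change after that. Subscript M is the MITI and A the avatar score.

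- MITI change = (start + w_M + a_M) − start = w_M + a_M.
- Avatar change = (start + w_A + a_A) − (start + w_A) = a_A.

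The term w_A cancels because it is already in the avatar starting value.

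**Step 3. What a_A is made of**

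- Repeat practice on the one simulation written for each project, with a coach that points to the better choice and an option to undo selections.
- Experience from delivering the intervention and, in one ACHIEVE-D arm, performance coaching.
- Loss of workshop gains, which Strengths says diminish within a few months.

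These components can pull in opposite directions. If decay outweighs practice, a is negative. Suppose for illustration that both measures respond alike, so that one w and one a apply to both. Then whenever −w < a < 0, avatar change is below zero while total change w + a is above zero. A fall in avatar score would be compatible with training that worked.

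**Step 4. Who contributes**

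A change score needs a first and at least one later completed simulation. The article reports 127 enrolled, but the avatar Overview only encourages registration, and Limitations expects that workload may restrict practice. The number contributing is therefore at most 127 and is not stated.

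**Step 5. The association**

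The Analytic Plan pairs MITI scores with a simulation from the same data collection window. Both measures are ticked at baseline, so a baseline pair is possible. On the sequence in step 1 it would join a value from before the workshop to one from after the module.

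**The case against.** **The MITI carries the skill inference.** The Analytic Plan assigns change in skill to the MITI and sets its one-point criterion for MITI global scores only. The Abstract's conclusion also depends on MITI scoring. This stands, and it limits the severity.

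**Limitations already warns about avatar scores.** It says they may not be a valid outcome because the same simulations serve training and assessment, and that the workshop alone cannot be isolated. This reduces the risk of misreading. It does not say that the avatar baseline follows the workshop, so the conflict remains.

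**Baseline plainly means the first simulation.** The Data Collection sentence cannot be literal for every measure. Measures also covers perceived usefulness of the avatar and end-of-project interviews, which Table 3 does not tick at baseline. This has force and makes the defect largely one of labelling. But the article nowhere gives that definition, and on that reading the avatar contrast still omits the initial gain.

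**Stronger readings that the article does not support.** A reader might infer any of the following:

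- That avatar change carries no trace of the workshop, or is nothing but repeat practice. Decay of workshop gains and field experience also fall within it.
- That all 127 practitioners are affected. Registration is only encouraged.
- That the gap between MITI and avatar change can be given in points. The article states no expected gain for either measure. Avatar global scores are also built from counts of targets and pitfalls, so the two scales are not interchangeable.
- That the association will include mismatched baseline pairs. The Analytic Plan does not say so, and its same-window rule might exclude them.

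**Conclusion.** The contradiction is real and nothing in the article resolves it. On the described sequence, the earliest avatar score comes after the workshop and the module. Change from it does not capture the initial gain from either, whereas MITI change does. This matters because the article uses both measures as evidence on both training approaches.

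Severity is moderate. The MITI analysis is unaffected, and the article already doubts the avatar score as an outcome, though for a different reason. The size of the omitted gain cannot be derived from the article. The conclusion rests on one assumption: that no undescribed avatar run takes place before training. If one does, the avatar change is a pre-post contrast after all, and the gap lies in the description of the procedure.

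**What to change.** 1. In Table 3 and Data Collection, label the avatar baseline as the first completed simulation after the workshop and didactic module. If a pre-training run does take place, describe it instead and reconcile the avatar Overview with it.
2. In the Analytic Plan, describe the avatar contrast as change during avatar practice after the workshop. State that it will not be read as the effect of the workshop or of the training as a whole.
3. Exclude from the MITI-avatar association any pair of a pre-training MITI score with a post-workshop avatar score.
4. Add the baseline timing to Limitations, beside the existing caution on avatar scores, and report how many practitioners have a first and at least one later completed simulation.

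The cost is wording, with no new data. The real loss is that the avatar outcome can no longer be presented as a pre-post training effect.

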## Results

The ALACRITY Center was funded in August 2018. Recruitment for the studies started in February 2021. We have enrolled 127 participants. We anticipate the projects will be completed in Spring 2023 and anticipate that the results will be reported in late 2023 or 2024.

## Discussion

### Overview

The treatment of CVD risk factors is a public health priority for persons with SMI who experience symptoms disproportionally owing to these chronic health conditions. In community mental health practices where patients regularly receive their care, providing physical health interventions using an MI approach has untapped potential [4]. However, practitioners in these facilities already have excessive demands on their time, a challenge exacerbated by staff shortages and turnover, and they may not have the time, energy, or organizational support to learn how to implement patient-centered CVD risk reduction interventions [18,19]. To overcome some of the barriers to wide-scale adoption of MI in these contexts, we have adapted the traditional MI training format and created brief videoconference workshops supplemented by postworkshop avatar-based practice simulations to prepare the practitioners to deliver 3 evidence-based health interventions in community mental health settings. We hope that these formats will be acceptable and lead to an uptake and improvement of practitioners’ patient-centered skills.

### Strengths

There are several strengths in this study. We created a tailored training that has shorter duration than traditional training as a way to expose busy practitioners to MI. Brief trainings (<8 hours) are more time efficient and have been shown to make some difference in physician consultation behavior [51]. We adapted the real-time training to be delivered remotely in shorter bouts of time. We aim to identify whether the brief trainings provided are adequate to prepare real-world clinicians to perform the EBP and subsequently assess their skill acquisition with a validated measure.

Although technology-based virtual reality training methods have been used in medical and other health professionals’ education, the use of avatars and other computer programs that provide interactive learning opportunities is not as common in behavioral health skills training [25,26,30,52-54]. Virtual platforms are a relatively new, potentially promising mode for training in MI and allow busy practitioners to learn the patient-centered counseling approach from expert trainers without having to travel to an off-site location. We incorporated 3 novel avatar conversation simulations tailored for practitioners to practice and receive feedback on their use of MI in simulated discussions about weight loss, smoking cessation, and cholesterol management. We will assess their acceptability to a wide range of practitioners at the end of each project.

We describe the study’s training content and development of the avatar simulations as well as 2 methods of measuring adherence to MI and assessing change in practice that results from the trainings provided. Research has shown that the immediate skill gains from a workshop training diminish within a few months and that postworkshop follow-up performance feedback with coaching is needed for practitioners to sustain or further improve MI skills [14,16,17,55]. Although our initial training is brief, the automated coaching and feedback offered during the avatar simulations should mirror the role of coaching as a way of providing follow-up training to improve learners’ skills. Simulation technology offers the capability to move beyond traditional in-person training and provide skill training through repeated practice and feedback [56].

### Limitations

One limitation of the study is that none of the training methods have a comparator condition. The pretest-posttest outcomes are used here to assess the acceptability, feasibility, and effectiveness of the 2 training methods for improving practitioners’ MI skills.

Avatar practice requires practitioners to set aside time during their busy workdays. The extra workload and responsibilities of staff during the COVID-19 pandemic may leave little time or motivation for avatar skills practice after their initial exposure to MI, thus potentially decreasing the impact of this component of the training.

Another limitation is that because of the nature of the avatar platform and how the 3 conversations simulations are built, there are limited choice options. Therefore, after a learner has used the platform a few times, they might find it redundant and be less willing to practice. The didactic module and the conversation simulations may be a great opportunity for novice learners to practice their skills; practitioners with more experience in patient-centered counseling may be less interested in using a platform that offers few multiple-choice conversation options.

To overcome the challenges of assessing MI skills in implementation settings, we are using multiple measures, namely, MITI and the automated feedback scores from the avatar simulations. The feedback feature of the avatar simulations was originally designed to assist learners in improving MI skills. The mapping approach we used to create the automated scoring system for each of the global scores may limit the precision of the measure to capture how well the clinician is using MI. In addition, because participants complete the same simulations for training and assessment purposes, scoring from the simulations may not be a valid outcome measure of their MI skills.

This study design was in the context of implementation research and does not allow us to examine the effect of the MI workshop training component alone. However, examining MI in real-world settings is an innovative aspect of the study. Although there are limitations to asking about experiences of the training over a 6- or 12-month period, our qualitative interviews at the end of the study will add detail to the quantitative results.

Although the development of our avatar conversation simulations included multiple iterations between our study experts and the developers of the platform, further advances in virtual training have become available since the study was first conceptualized. Other programs that allow for additional branching conversation scripts could be integrated into future versions of this training to better support virtual learning [57]. Virtual reality programs that create endless iterations of interactive experiences such as those offered by SIMmersion are another option to promote learning. Platforms that use natural language processing with actual recorded patient encounters also have the potential to offer feedback to learners on their MI skills and could be an addition to MI training for busy mental health practitioners [56,58].

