**Methods:**

Clinicians and staff in community mental health clinics across Maryland were trained to deliver 3 distinct evidence-based physical health lifestyle interventions using an MI approach to persons with SMI. The real-time brief MI workshop training for ACHIEVE-D weight loss coaches was 4 hours; IMPACT smoking cessation counselors received 2-hour workshops and prescribers received 1-hour workshops; and RHYTHM CVD risk reduction program staff received 4 hours of MI. All workshop trainings occurred over videoconference. The asynchronous avatar training includes 1 common didactic instructional module for the 3 projects and 1 conversation simulation unique to each study’s target behavior. Avatar training is accessible on a commercial website. We plan to assess practitioners’ attitudes and beliefs about MI and evaluate the impact of the 2 MI training approaches on their MI skills 3, 6, and 12 months after training using the MI Treatment Integrity 4.2.1 coding tool and the data generated by the avatar-automated scoring system.

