### MI Training

MI Training for the ALACRITY Center studies consists of 2 distinct approaches: real-time brief workshop training over videoconferencing and asynchronous avatar training.

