##### Development

Owing to the advent of the COVID-19 pandemic, all MI trainings were modified from an in-person format to delivery over videoconferencing. Although there is not much known about how best to adapt the content of in-person experiential training workshops for this purpose, MINT members communicated ideas for the transition on the e-forum of their listserve [38]. Additional ideas for modifying training activities were offered during workshops, and a monthly virtual trainers meeting for sharing activities, ideas, and successes is ongoing for any interested MINT member. As a result of participation in these various collaborative conversations, the first author ([name]) modified several training activities for the videoconferencing format. One key consideration was how best to engage participants and encourage them to try different components of the MI method while being observed by others on screen rather than in the privacy of small groups. The trainer incorporates multiple activities, alternating training techniques to keep learners interested, including the use of written transcripts with change talk and sustain talk indicated in different colored fonts and small breakout rooms for practice exercises [39,40]. Efforts are made to switch styles every 20 minutes to best engage learners. Anonymous polling provides low-stakes opportunities for learners to select the most MI-consistent practitioner strategy in response to a vignette (eg, choose an evocative question, select the reflective listening statement, or identify the best example of a collaborative information exchange); the chat function allows the trainees, who may be less comfortable or quick to respond, opportunities to pose questions or respond to trainer requests.

All synchronous, real-time trainings will be held over videoconference and scheduled at a time that accommodates most practitioners at each site. As it is challenging to synchronize participants from multiple sites where the research is being conducted, for anyone unable to attend the real-time meeting, recorded Zoom sessions (Zoom Video Communications) will be made available for viewing. The first author developed a tailored handout resource packet with specific examples of how to use MI when discussing each project’s target behavior change; this material will be provided to practitioners to further support their MI skill acquisition during and after training.

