### Conclusions

This study will help us understand the effectiveness of 2 scalable training strategies on practitioners’ use of MI and how these approaches impact practitioners’ beliefs about, the importance of, and their confidence to use MI when delivering 3 interventions focused on CVD risk reduction to patients with SMI. The degree of tailoring to specific lifestyle change targets and the amount of real-time interaction needed to garner training effects in MI are not known; this research will contribute to knowledge about the effectiveness of brief videoconferences for training community mental health practitioners in MI. Testing MI skill uptake from videoconference training sessions has not been documented in the literature; this project will be a step forward in filling this gap. The study will also provide information about the perceived usefulness of the avatar as a modality for learning MI. On the basis of our results of this study, a logical next step to determine the most effective scalable training approach would be an RCT that compares different MI training modalities and includes a comparator condition.

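### The article claims it will show the effectiveness of each of 2 training methods on MI skills, but its schedule can estimate only one uncontrolled before-after change under the combined training

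*Protocol article*

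**What the plan says.** The MI Training section presents the components as separate: "MI Training for the ALACRITY Center studies consists of 2 distinct approaches", the videoconference workshop and the avatar.

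Three places promise a result on their effect:
- The Abstract (Methods) plans to "evaluate the impact of the 2 MI training approaches on their MI skills 3, 6, and 12 months after training".
- The Limitations section says the pretest-posttest outcomes are "used here to assess the acceptability, feasibility, and effectiveness of the 2 training methods".
- The closing Conclusions open with "This study will help us understand the effectiveness of 2 scalable training strategies". They go on to single out brief videoconferences as something whose effectiveness the study will inform, and describe skill uptake from videoconference sessions as a literature gap that the project helps to fill.

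Other places say less:
- The Limitations section also states that no training method has a comparator and that the design "does not allow us to examine the effect of the MI workshop training component alone".
- The Abstract's Conclusions refer to brief training with avatar practice added to it, that is, to the package.
- The closing Conclusions leave the comparison of modalities to a later randomised trial.

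On timing, Data Collection and Table 3 place the MITI before training and then at 3 and 6 months, with a 12-month assessment in IMPACT and RHYTHM only. The avatar Overview opens platform access once the workshop is finished and asks practitioners to "complete their first conversation simulation as soon as possible after the real-time MI training".

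**The concern.** A before-after design can attribute a change to a component only if some measurement separates that component from the rest, or some comparison group lacks it. Here the two components are delivered back to back and the next MITI comes about 3 months later. If scores rise, the promised conclusion would credit the workshop, the avatar, or both separately, and the data could not say which.

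The practical stake is adoption. A mental health programme could take up the workshop without the avatar, or the reverse, on evidence that addresses only the two together. The article's own Strengths section sharpens this. It notes that workshop gains fade within a few months unless followed by coaching, and expects the avatar to take the coaching role. A 3-month MITI cannot tell a workshop effect that lasted from one that faded and was restored by avatar practice.

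**Working it through.** The article gives no figure to reproduce. The question is which effects the planned visits can identify, and it can be checked from the schedule.

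**Inputs**
- MITI visits: baseline, 3, 6 and (IMPACT, RHYTHM) 12 months (Data Collection, Table 3).
- Order: workshop, then avatar access, with the first simulation requested promptly (avatar Overview).
- Comparator: none for either method (Limitations).
- Planned contrast: MITI change from baseline to each later time point (Analytic Plan).

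**Model.** Mean MITI = a + w·W + v·A, where W = 1 once the workshop has been given and A = 1 once the avatar is available.

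| Visit | Intercept | W | A |
|---|---|---|---|
| Baseline | 1 | 0 | 0 |
| 3 months | 1 | 1 | 1 |
| 6 months | 1 | 1 | 1 |
| 12 months | 1 | 1 | 1 |

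**Result as planned.** The W and A columns are identical, so the rank is 2 of 3. Only w + v can be estimated; w and v cannot. Letting the effects differ by visit does not help, because each visit supplies one change for two unknowns.

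**By training group.** Fitting the four groups of Table 1 separately gives rank 4 × 2 = 8 out of 4 × 3 = 12. The same aliasing occurs in each group, so differences between projects do not rescue it.

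**Illustration.** The Analytic Plan takes 1 point on a MITI global score as the relevant change. If w + v = 1.0, then (w, v) = (1.0, 0), (0.5, 0.5) and (0, 1.0) all fit the planned data equally well.

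**What would separate the steps.** One MITI after the workshop and before avatar access adds the row (1, 1, 0), and the rank becomes 3 of 3. If a common post-baseline term (retest or secular change) is also allowed, that term equals W and the rank is 3 of 4. The workshop step would then remain uncontrolled without a comparator.

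**What is left.** For each MITI score there is one combined change per project and follow-up: 2 in ACHIEVE-D, 3 in IMPACT and 3 in RHYTHM, so 2 + 3 + 3 = 8. Each also contains the project's own training and, in ACHIEVE-D, the randomised performance coaching described in the Implementation Pilot Studies Overview.

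**The case against.** The strongest reply is that the limit is disclosed. The Limitations section states the lack of a comparator and the inability to isolate the workshop, the closing Conclusions defer comparison of modalities, and the Abstract's Conclusions use package wording. Effectiveness of 2 methods might also be read jointly, and the Analytic Plan lists only changes from baseline, with no step that attributes change to either component. This stands in part: the limit is not concealed, and the point is one of inconsistent wording. It does not remove the point, because the closing Conclusions still single out videoconferences after the Limitations have ruled that out.

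A second reply is that the aliasing concerns avatar availability, while actual use is voluntary, tracked and likely to vary. That is correct. But use is self-selected, so a relation between use and MITI change would be descriptive. Automated avatar scores do not fill the gap either, since the Limitations section doubts their validity as an outcome.

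A reader might be tempted to go further in three ways that the article does not support:
- **Recording viewers are analysed as live attendees.** The article offers "for anyone unable to attend the real-time meeting, recorded Zoom sessions", but does not say how their viewers will be classified, and it tracks live attendance.
- **The lack of an analysis by exposure is a defect.** A condensed article may leave that to the full protocol or analysis plan.
- **Avatar session counts cannot be compared across projects.** The same minimum of monthly practice applies everywhere, so the recommended minimum matches at the shared 3- and 6-month visits. Only end-of-study totals differ, because follow-up lengths differ.

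**Conclusion.** The point holds as a contradiction about effectiveness on MI skills. The Abstract Methods, one sentence of the Limitations and the closing Conclusions claim a property that the design lacks, while another sentence of the Limitations and the Abstract's Conclusions describe it correctly. From the stated MITI schedule, 0 of 2 component effects can be estimated; what can be estimated is their sum, without a control.

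This rests on the schedule as published (no MITI between workshop and avatar access) and on avatar access opening well before the 3-month visit, as the avatar Overview indicates.

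It would be wrong to infer that nothing can be learned about each method. Perceived usefulness of the avatar is surveyed, interviews cover both modalities, and attendance and avatar use are tracked, so acceptability and feasibility can be reported separately.

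**What to change.** Reword the Abstract Methods, the effectiveness sentence in the Limitations and the closing Conclusions so that all three describe an uncontrolled before-after change in MI skills under brief workshop training combined with avatar practice, delivered within each project. Remove statements on the effectiveness of each method, or of videoconferences alone. Keep the per-method wording for acceptability, feasibility and perceived usefulness.

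Optionally, describe MITI change by tracked live attendance and by the number of avatar sessions completed before each interview, separately by project, labelled exploratory and non-randomised.

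An added MITI between workshop and avatar access would separate the two steps, but it comes too late for the 126 practitioners whose training the Abstract reports as implemented, and it would still leave both steps uncontrolled. It belongs in the design of a later study.

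The cost is editing, plus one or two descriptive tables from data already tracked if the option is taken. The downside is a narrower headline claim.
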